### Secondary endpoint

1.3

The first secondary outcome to evaluate is the sensitivity/specificity of the pH test compared to the current Gold Standard (chest X-ray), also in consideration of clinical variables such as: food intake (time calculated in minutes from the last food intake, guaranteeing a minimum time to perform the test of at least 1 h) and taking drugs that affect gastric pH (proton pump inhibitors and antacids). Secondly, to evaluate the tolerance of the different NGT models used through pain monitoring (evaluated through the NRS scale at 24-48-72 h after placement and where an NRS score greater than ≥3 will be considered as a threshold value to identify poor tolerance). Thirdly, to evaluate the starting time of nutritional therapy from the request for placement of the NGT by the attending physician (calculated in minutes). Lastly, to evaluate possible complications associated with the positioning of the NGT and arising during the hospitalization period, such as: 1) mispositioning of the NGT (assessed with Chest X-ray); 2) tracheobronchial aspiration; 3) aspiration pneumonia 4) lesions of the oesophageal mucosa and of the upper airways (for points 2,3,4 evaluations by clinical examination, blood tests and instrumental tests requested by the attending physician).

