### Study procedures

2.2

Participants will be enrolled in three study arms, assigned according to the defined randomization criterion, to evaluate three different NGT models along with the use of an electronic pH meter. The first NGT is the *NUTRICIA FLOCARE PUR TUBE CH14 double lumen*, which features an additional lumen to the nutritional lumen specifically for pH aspiration. The other two NGTs are the *INNOVAMEDICA single lumen CH10 AVANOS_ST CH10* and the *INNOVAMEDICA single lumen CH12 AVANOS_ST CH12*, which have a single lumen. In all three study arms, the determination of the correct positioning (primary outcome) will take place through the monitoring of the gastric pH (gastric aspirate 5 ml; pH value ≤ 5.5)^46^ through the use of an electronic pH meter (pH Strips & Reader Innovamedica model pH X-act) which will be compared with the CXR (current gold standard). The comparison with the CXR will allow to evaluate the sensitivity and specificity of the pH test. An important aspect of the study is the evaluation of the time efficiency in starting nutritional therapy. This is measured in minutes and aims to determine if the pH test can reduce the time taken for NGT positioning evaluation compared to the current 1440 min required for chest X-ray assessments. The time frame is obtained from the evaluation of the service at IRCSS Humanitas Research Hospital. Furthermore, Patient tolerance to the NGT will be assessed at 24, 48 72 h post-placement using the NRS scale. This will help identify pain levels and characteristics, to evaluate whether different NGT calibers (CH) affect patient tolerance. Throughout the entire period of hospitalization of the patient, complications associated with the positioning of the NGT will be recorded. These include mispositioning of the NGT (assessed by chest x-ray); tracheobronchial aspiration; aspiration pneumonia; lesions of the oesophageal mucosa and upper airways (assessed by clinical examination and instrumental tests requested by the attending physicians). During the post-clinical phase, an economic analysis will be conducted to evaluate potential cost savings from using the pH test for correct NGT positioning, with respect to X-ray use. This includes analysing costs of auxiliary personnel (based on transport times to radiology, calculated as Euro/hour), professional fees for performing chest Xrays, and the cost of the Xrays themselves. A graphical representation of the study procedures is depicted in Fig. 1.

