#### Determination of sample size

2.5.1

Under the hypothesis that with standard method only 42 % of catheter positioning of the NGT allow the measurement of the pH of the gastric aspirate, we want to demonstrate, with a power of 80 % and a type I error of 5 % that the 3 studied NGT allow measurement of pH in at least 62 % of positioning. Therefore, the study need 47 patients in each arm. These numbers were gathered from the current data available at IRCCS Humanitas Research Hospital. This sample size also allows us to see a difference in discomfort between the three study groups as the difference in NGT calibre could be tolerated differently (NRS scale). Following this analysis, a total of 150 patients, subdivided into 50 patients per branch, have to be included in the study.

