#### Statistical analysis

2.5.3

Continuous variables following a symmetric distribution will be presented with mean (SD), while skewed variables will be presented with median (IQR). Ordinal variables will be presented with median (IQR) and categorical variables will be presented as n (%). For primary endpoint, the percentage of catheter positioning allowing pH measurement will also be described with 95 % confidence interval. Differences among the three groups will be explored with chi square test for categorical variables, or one-way ANOVA or Kruskal Wallis test, for continuous variable, depending on their distribution shape. MP patients will also be analysed in order to explore the existence of a different pH threshold to identify the correct catheter positioning in case of use of antiacids-PPIs drugs. All analysis will be performed with Stata version 17 or superior. Statistical significance was set to p < 0.05.

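### Read literally, the tolerance comparison between tubes rests on the NRS cut at about 3; comparing the full score would usually detect more, with no extra data

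*Protocol article*

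**What the plan says.** Section 1.3 (Secondary endpoint) measures tolerance through pain, "evaluated through the NRS scale at 24-48-72 h after placement", and adds that "an NRS score greater than ≥3 will be considered as a threshold value to identify poor tolerance". The wording joins a strict inequality to a ≥ sign, so it does not settle whether a score of exactly 3 counts as poor tolerance.

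Section 2.2 (Study procedures) describes the purpose in terms of levels: "This will help identify pain levels and characteristics, to evaluate whether different NGT calibers (CH) affect patient tolerance".

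Section 2.5.1 (Determination of sample size) derives the arm size from the primary endpoint and then states: "This sample size also allows us to see a difference in discomfort between the three study groups". It mentions the NRS scale there but gives no effect size, SD, rate or power for it.

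Section 2.5.3 (Statistical analysis) says "Differences among the three groups will be explored with chi square test for categorical variables, or one-way ANOVA or Kruskal Wallis test, for continuous variable". Ordinal variables appear only under presentation: "Ordinal variables will be presented with median (IQR"). They have no between-group test.

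**The concern.** The NRS is an ordered score recorded for every patient. The only tolerance criterion the article defines turns it into two categories, and a categorical variable goes to chi-square under section 2.5.3. With the cut read as ≥3, a patient scoring 3 then counts the same as one scoring 9, and a fall from 6 to 3 or from 2 to 0 counts as no change. The article cites no source for the cut, and no decision in it needs a yes/no status for each patient.

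Tolerance is not incidental here. Section 2.2 uses it to judge the effect of calibre, section 3 uses it to help choose between tubes, and section 2.5.1 says the sample size supports the comparison. If a less sensitive analysis finds no difference, the tubes may be reported as equally tolerated when they are not. Sensitivity would also depend on where typical scores lie relative to 3, which the article does not state.

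**Working it through.** **The plan's own figure.** The only sample-size figure concerns the primary endpoint: 42% against 62%, power 80%, type I error 5%, 47 per arm. As a two-sided one-sample test against a fixed 42%:

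n = [1.960·√(0.42·0.58) + 0.842·√(0.62·0.38)]² / 0.20² = (0.967 + 0.409)² / 0.04 ≈ 47.3.

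The stated 47 is therefore reproduced, but nothing in it refers to the NRS.

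**Inputs for tolerance.** From the documents: three arms, 50 per arm, significance at p < 0.05, cut at about 3. Assumed, because the article does not give them: a 0–10 range, one measurement time, and the means, SDs and shapes below.

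**Method.** Trials were simulated with normal scores rounded and clipped to 0–10. Kruskal-Wallis on the score was compared with a 3×2 chi-square on the cut, read both as ≥3 and as >3, with 5,000 runs per scenario. The lowest arm mean ran from 1 to 4, the SD from 1.5 to 2.5, and the largest arm difference was 1.0 or 1.5 points. Either one arm differed or the arms followed a linear trend. That makes 48 scenarios. With no true difference, the rejection rates were 5.1% (Kruskal-Wallis) and 4.3% (chi-square).

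| Means | SD | Kruskal-Wallis | Chi-square, ≥3 | Chi-square, >3 |
|---|---|---|---|---|
| 2 / 2 / 3 | 2 | 69% | 52% | 50% |
| 2 / 2.5 / 3 | 2 | 55% | 40% | 38% |
| 3 / 3 / 4 | 2 | 70% | 49% | 53% |
| 4 / 4 / 5 | 2 | 69% | 34% | 48% |
| 2 / 2 / 3 | 2.5 | 48% | 35% | 35% |
| 1 / 1 / 2 | 1.5 | 90% | 72% | 51% |
| 4 / 4 / 5 | 1.5 | 91% | 41% | 70% |

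**Summary of the 48 scenarios.**
- The median loss from cutting is 16 points at ≥3 (range 1 to 50) and 17 points at >3 (range 1 to 44).
- Among the 24 scenarios with a 1-point difference, the loss at ≥3 is 10 to 20 points in 14, above 20 in 9 and below 10 in 1.
- The smallest losses, near 1 point, come from 1.5-point differences with SD 1.5, where both tests already exceed 98%.
- The last two table rows show that the reading of the cut alone can move power by 20 to 30 points.

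**Skewed scores.** Six gamma-Poisson scenarios with a 1-point range across arms lost about 5 to 11 points. Gamma scores with the SD held at 2 lost 22 points for means 2/2/3 (92% against 70%) and 8 points for means 3/3/4 (83% against 75%).

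**A case that goes the other way.** Suppose tolerant patients score uniformly on 0–2, intolerant patients uniformly on 3–6, and only the share of intolerant patients differs between arms. The cut at ≥3 then wins:
- 10/10/30% intolerant: chi-square 77%, Kruskal-Wallis 44%.
- 20/20/40% intolerant: 63% against 43%.
- 30/30/50% intolerant: 57% against 43%.

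This setting puts the boundary between the two kinds of patient exactly at the cut. As their scores overlap, the advantage shrinks. In one overlapping setting it reversed: Kruskal-Wallis 25%, chi-square 13%.

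**The case against.** The strongest objection is that the article nowhere says tolerance will be tested by chi-square. Section 1.3 can be read as a flag for individual patients. Section 2.2 speaks of pain levels, section 2.5.1 ties the discomfort difference to the NRS scale and not to the cut, and section 2.5.3 lists Kruskal-Wallis. Which form of a secondary endpoint gets which test is often left to an analysis plan, and none is shown. This stands in part. A reader might infer that the plan commits to the dichotomy alone, and the documents do not support that. The dichotomy is only the literal route, because it is the one defined tolerance criterion and ordinal variables have no test.

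Second, a reader might infer a fixed power loss, such as a narrow band that holds in most settings. The documents give no NRS distribution, and the simulated losses spread too widely for that. Only an assumption-dependent range is defensible.

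Third, the proportion with poor tolerance is a legitimate and readable outcome, and the cut can be the more powerful analysis. Both statements are true. The second needs the arms to differ only in the share of patients beyond a boundary at the cut, and nothing in the article suggests that pattern. The first is met by keeping the percentage as a reported result.

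**Conclusion.** The point holds as an inexpensive improvement to a secondary analysis. On the literal reading, the tube comparison for tolerance uses a dichotomised score with an ambiguous cut, while the ordered score that is already collected has no assigned test.

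Under assumed shifts of the whole distribution by about 1 point, with 50 per arm, dichotomising typically costs about 10 to 20 points of power. The range is about 1 to 50 over the means, SDs, shapes, shift sizes and readings of the cut that were tried. The direction favours the full score in every shift scenario, and it reverses only in the special mixture described above.

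This does not show that the trial is too small for the tolerance comparison. The article gives no effect size against which its sample-size statement could be tested.

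**What to change.** In sections 1.3 and 2.5.3:
- State that the between-tube tolerance comparison uses the full NRS score, by Kruskal-Wallis or a proportional-odds model across the three arms.
- Add ordinal variables to those tested by Kruskal-Wallis.
- Word the cut so that it has one meaning, and report the percentage above it per arm with a 95% CI as a descriptive supplement.

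The cost is one or two sentences, with no new data, visits or patients. The small downside is that a shift in score is less direct to explain than a percentage, which is still reported.

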### Other outcomes of interest

1.4

Evaluation of cost reduction compared to the current gold standard (chest radiography). Costs related to the entire NGT placement procedure (cost of NGT, personnel, clinical procedure for monitoring correct placement) will be evaluated. This calculation will be expressed in Euros.

### Safety outcomes

1.5

At each placement of NGT, a check will be carried out by means of a pH test with an electronic pH meter associated with a chest x-ray in order to evaluate the correct or not correct positioning of the device.

## Methods

2

### Study design

2.1

This study is a randomized clinical trial regarding the efficacy of different NGTs in aspiring gastric secretions so as to assess correct NGT placement by pH monitoring and reduce the use of chest X-ray (CXR) in everyday clinical practice.

### Study procedures

2.2

Participants will be enrolled in three study arms, assigned according to the defined randomization criterion, to evaluate three different NGT models along with the use of an electronic pH meter. The first NGT is the *NUTRICIA FLOCARE PUR TUBE CH14 double lumen*, which features an additional lumen to the nutritional lumen specifically for pH aspiration. The other two NGTs are the *INNOVAMEDICA single lumen CH10 AVANOS_ST CH10* and the *INNOVAMEDICA single lumen CH12 AVANOS_ST CH12*, which have a single lumen. In all three study arms, the determination of the correct positioning (primary outcome) will take place through the monitoring of the gastric pH (gastric aspirate 5 ml; pH value ≤ 5.5)^46^ through the use of an electronic pH meter (pH Strips & Reader Innovamedica model pH X-act) which will be compared with the CXR (current gold standard). The comparison with the CXR will allow to evaluate the sensitivity and specificity of the pH test. An important aspect of the study is the evaluation of the time efficiency in starting nutritional therapy. This is measured in minutes and aims to determine if the pH test can reduce the time taken for NGT positioning evaluation compared to the current 1440 min required for chest X-ray assessments. The time frame is obtained from the evaluation of the service at IRCSS Humanitas Research Hospital. Furthermore, Patient tolerance to the NGT will be assessed at 24, 48 72 h post-placement using the NRS scale. This will help identify pain levels and characteristics, to evaluate whether different NGT calibers (CH) affect patient tolerance. Throughout the entire period of hospitalization of the patient, complications associated with the positioning of the NGT will be recorded. These include mispositioning of the NGT (assessed by chest x-ray); tracheobronchial aspiration; aspiration pneumonia; lesions of the oesophageal mucosa and upper airways (assessed by clinical examination and instrumental tests requested by the attending physicians). During the post-clinical phase, an economic analysis will be conducted to evaluate potential cost savings from using the pH test for correct NGT positioning, with respect to X-ray use. This includes analysing costs of auxiliary personnel (based on transport times to radiology, calculated as Euro/hour), professional fees for performing chest Xrays, and the cost of the Xrays themselves. A graphical representation of the study procedures is depicted in Fig. 1.

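### The trial has no concurrent pH-versus-X-ray contrast for time, so the stated aim of showing time saved by the pH test rests on one historical figure of 1440 min

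*Protocol article*

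**What the plan says.** All references are to the protocol article.

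- **Time endpoint (section 1.3).** The third secondary outcome is to "evaluate the starting time of nutritional therapy from the request for placement of the NGT by the attending physician", in minutes.
- **Stated aim (section 2.2).** The same measure is introduced as time efficiency in starting nutrition. The section then says that it "aims to determine if the pH test can reduce the time taken for NGT positioning evaluation compared to the current" figure. The full comparator phrase is "compared to the current 1440 min required for chest X-ray assessments". Its source: "The time frame is obtained from the evaluation of the service at IRCSS Humanitas Research Hospital".
- **Verification (sections 1.5 and 2.2).** Each placement is checked by both methods: the pH is tested "with an electronic pH meter associated with a chest x-ray in order to evaluate the correct or not correct positioning of the device". The pH method is common to the arms: "In all three study arms, the determination of the correct positioning (primary outcome) will take place through the monitoring of the gastric pH". Only the tube differs.
- **Analysis (section 2.5.3).** Continuous variables are compared among the three groups by one-way ANOVA or Kruskal-Wallis. No other comparison of times is listed.
- **Current practice (section 1, Introduction).** The hospital already tests pH first and turns to X-ray when that fails. The pH-based procedure succeeded in 42% of placements.

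**The concern.** The question in section 2.2 is about verification methods: is the pH test quicker than the X-ray? The randomised contrast is about tubes. A three-group test of request-to-feeding time can show whether one tube leads to earlier feeding than another. It cannot attribute time saved to the pH test, because all three arms have the pH test and all three have the X-ray.

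That leaves the 1440 min as the only reference for the stated aim. Two misreadings are then possible. A real saving may not appear, because the X-ray wait is in every patient's time. Or a large apparent saving may be reported against a figure that does not describe what patients at this hospital now experience. Section 2.2 calls the time evaluation an important aspect of the study, and section 3 calls the metric crucial, so a result that cannot bear its interpretation would matter.

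**Working it through.** **1. Is there a concurrent contrast?** Section 1.5 puts both checks at every placement, and section 2.2 gives all arms the same pH meter and the same X-ray comparison. No arm is verified by X-ray alone or by pH alone. Section 2.5.3 compares tubes. So there is no between-arm contrast of pH with X-ray, and no within-patient contrast of the two times is described.

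**2. What would request-to-feeding time show?** The article does not say which result releases feeding, so both cases are needed.

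- *Feeding waits for the X-ray.* Each patient's time includes the wait for the X-ray, however early the pH result came. Any saving from the pH test is hidden.
- *Feeding is released on the pH result.* The observed times can be set beside 1440 min, but only descriptively. That figure is a single value (exactly 24 h) given without a spread or number of patients. The events that start and end it are not defined. Section 1.3 runs from request to start of nutrition, while one phrase in section 2.2 speaks of positioning evaluation, so it is unclear whether the intervals match.

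**3. Does 1440 min represent current practice?** The plan gives no derivation to reproduce. Inputs: 42% pH success now (section 1), 62% as the target (section 2.5.1), 1440 min for X-ray-verified patients (section 2.2). The time *t* for pH-verified patients is not in the article, and 0 to 240 min is assumed.

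Mean time = p × t + (1 − p) × 1440, where p is the proportion verified by pH.

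| | t = 0 | t = 240 |
|---|---|---|
| Current mix, p = 0.42 | 0.58 × 1440 = 835.2 | 100.8 + 835.2 = 936.0 |
| 1440 minus current mix | 604.8 | 504.0 |
| Target mix, p = 0.62 | 0.38 × 1440 = 547.2 | 148.8 + 547.2 = 696.0 |
| 1440 minus target mix | 892.8 | 744.0 |
| Current mix minus target mix | 288.0 | 240.0 |

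On these assumptions, existing practice would already look about 504 to 605 min better than 1440. A rise from 42% to 62% would look like a saving of 744 to 893 min against 1440, but of 240 to 288 min against the current mix. The ratio is 0.62/0.20 = 3.1 whatever *t* is.

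One simplification: section 2.5.1 uses 42% and 62% for placements where pH can be measured, and the table treats all of them as confirmed.

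**4. Which summary suits a paired analysis?** Not every measurable aspirate will read pH ≤ 5.5. If an assumed 70% to 90% do, 0.62 × 0.70 = 43% to 0.62 × 0.90 = 56% of patients are confirmed by pH. The remaining 44% to 57% have a difference of zero by rule. The median could therefore be zero even when confirmed patients gain many hours, and the mean is the more informative summary.

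**The case against.** The strongest reply has four parts.

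*Dual verification is deliberate.* It is needed for the sensitivity and specificity of the pH test and for safety. That is right, and the X-ray in every patient is not a flaw. The difficulty lies in the time claim attached to the design.

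*A journal article may leave the feeding-release step and the CRF time fields to the full protocol, and the procedures figure is not shown.* This stands. A reader might infer that the endpoint cannot show any saving, or that the observable saving is 0 min. That holds only if feeding waits for the X-ray, which the article does not state. Settling the release rule would still not supply a concurrent comparator.

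*No formal test against 1440 min is planned.* Also right: section 2.2 states an aim, and section 2.5.3 lists only three-group comparisons. The figure may already be meant as description, but the plan then has no analysis that answers its stated aim.

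*The figure comes from the recruiting hospital.* It is historical, but nothing shows that it describes a different kind of patient.

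Two further inferences are tempting and unsupported. One is that nearly all of the 1440 min would be saved. That ignores patients without a confirming pH, who still need the X-ray. The other is that the cost outcome fails in the same way. Section 1.4 already covers the whole procedure, including tube, personnel and monitoring of placement, and the X-ray-related items in section 2.2 are introduced as inclusions rather than a complete list.

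**Conclusion.** The point holds as a matter of design and interpretation for one secondary endpoint that has no stated power. The trial can compare tubes on request-to-feeding time. As described, it has no concurrent basis for saying that the pH test shortens confirmation relative to X-ray, and the 1440 min figure cannot fill that gap.

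The size is illustrative. With X-ray-verified patients at 1440 min and pH-verified patients at an assumed 0 to 240 min, current practice averages about 835 to 936 min, so 1440 min overstates the present position by about 504 to 605 min. The conclusion about the missing contrast does not depend on that assumption. The primary endpoint is unaffected. The change is worth making because the X-ray in every patient makes a better comparison available at little cost.

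**What to change.** - Record four times in each patient: request for the tube, pH result, X-ray report and start of feeding.
- Make the pH-versus-X-ray time analysis the within-patient difference: request to X-ray report minus request to pH result. Set it to zero where no pH ≤ 5.5 is obtained.
- Report the mean difference with a bootstrap 95% CI, together with the proportion confirmed by pH. Do not report the median alone.
- Keep request-to-feeding time as a comparison between tubes, and 1440 min as description only.
- Reconcile the interval wording in sections 1.3 and 2.2, and define the start and end of the 1440 min. Which result releases feeding is for the sponsor to state.

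The cost is a few extra CRF time fields and one paired analysis, with no change to patient care. The fields should be in place before enrolment, since times not captured prospectively may be hard to recover. One limitation should be noted in the plan: if the study X-ray loses urgency once a pH result is available, its report may come later than in routine care and the paired difference would be too large.

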### Study Objectives

1.1

The aim of this study is to evaluate the placement of NGT for nutritional purposes according to the best standards of safety and quality by developing a multidisciplinary protocol for this procedure. Through the use of NGTs that can guarantee greater aspiration performances with the same caliber, it would be possible to have a better aspiration of the gastric aspirate (≥5 ml) which would guarantee the possibility of carrying out the pH test in order to ensure correct positioning of the NGT.

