## Implications and Perspectives

3

According to international guidelines, the correct positioning of a NGT may be checked by testing the pH of aspirate, or by X-ray. The pH test method is preferrable due to lower costs as well as absence of radiation exposure for the patient. Unfortunately, pH testing is not always feasible, often due to difficulties in aspiration of current NGTs. By using new generation NGTs, designed for better aspiration but with the same, or even smaller, calibre as classical NGTs, it may become possible to more frequently avoid X-ray confirmation of NGTs insertion, without adding any additional burdens on the patients. The use of an electronic pH meter allows for more accurate measurements, which should translate to greater certainty in positioning as well as avoiding dubious results that may otherwise be an indication for X-ray. By checking correct positioning by X-ray we will further assess the sensitivity and specificity of pH testing for NGTs placement. Differentiation between the three possible latest-generation NGTs will not only look at aspiration potential, but also patient tolerability and adverse events, in order to avoid recommending NGTs that may turn out to be impractical in everyday clinical use. In particular, smaller calibre NGTs may allow for less patient discomfort, and subsequently greater compliance, ease of treatment and fewer nutrition-related adverse events. The main limitation of the study may be encountered with patients under antacid or PPI therapy, for which correct placement may give readings above pH 5.5, which are an indication for X-ray confirmation of correct placement. Unfortunately, no clinical trials exist that provide evidence on how to mitigate such factors, so we will gather data regarding possible confounding factors.

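### The protocol says the NRS data will show whether calibre affects tolerance, but the CH14 tube also differs in lumen number and product line, so only CH10 versus CH12 can support a calibre conclusion.

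*Protocol article*

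**What the plan says.** The protocol article words the tolerance question in two ways.

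- **As a calibre question.** Section 2.2 (Study procedures) says NRS is recorded at 24, 48 and 72 h "to evaluate whether different NGT calibers (CH) affect patient tolerance". Section 2.5.1 (Determination of sample size) says the sample size also suffices to see a discomfort difference between the three groups, and gives their differing calibre as the reason. Section 3 (Implications and Perspectives) anticipates the direction: "In particular, smaller calibre NGTs may allow for less patient discomfort".
- **As a question about tube models.** Section 1.3 (Secondary endpoint) defines the aim as "to evaluate the tolerance of the different NGT models used through pain monitoring", with an NRS threshold of 3 for poor tolerance.

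Section 2.2 defines the arms as "NUTRICIA FLOCARE PUR TUBE CH14 double lumen", "INNOVAMEDICA single lumen CH10 AVANOS_ST CH10" and "INNOVAMEDICA single lumen CH12 AVANOS_ST CH12". It describes the first tube as one "which features an additional lumen to the nutritional lumen specifically for pH aspiration". Section 2.2.5 adds that the two single-lumen tubes are made of particular materials intended to improve performance.

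Section 2.5.3 plans tests across the three groups: chi-square for categorical variables, and ANOVA or Kruskal-Wallis for continuous ones. It names no contrast for calibre.

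**The concern.** To attribute a difference to calibre, the arms compared should differ in calibre and, as far as the documents describe, in nothing else. Between CH14 and either other arm, calibre, number of lumens and product line all change together. Randomisation balances the patients across arms, but it cannot separate features that are built into the same tube.

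What is at stake is the conclusion. Suppose CH14 is worse tolerated and the three-group test is significant. The result would match the expectation in sections 2.5.1 and 3 and could be reported as a calibre effect, although the second lumen or the make and material of the tube could equally explain it. A recommendation to use smaller tubes for comfort would then rest on a contrast that does not isolate size.

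**Working it through.** **1. The plan's own figure.** Section 2.5.1 gives 47 patients per arm for 42% versus 62%, 80% power and 5% type I error. A one-sample test against a fixed 42%, two-sided, gives

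n = [(1.960·√(0.42·0.58) + 0.842·√(0.62·0.38)) / 0.20]² = [(0.967 + 0.409) / 0.20]² = 47.3.

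The stated 47 therefore reproduces to within rounding. This calculation concerns aspiration success and has no bearing on tolerance. Section 2.5.1 gives no effect size or SD for NRS.

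**2. What each contrast varies** (arm definitions from section 2.2; a shared product line is read from the shared product name)

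| Contrast | Calibre | Lumens | Product line |
|---|---|---|---|
| CH10 vs CH12 | differs (2 CH) | same (single) | same |
| CH10 vs CH14 | differs (4 CH) | differs | differs |
| CH12 vs CH14 | differs (2 CH) | differs | differs |

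Two of the three contrasts mix calibre with the other two features.

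**3. The same check in matrix form.** Take an intercept, indicators for CH12 and CH14, an indicator for double lumen and an indicator for product line. The three arms give the rows (1,0,0,0,0), (1,1,0,0,0) and (1,0,1,1,1). The rank is 3 for 5 columns, and the last three columns are identical, so the effects of CH14, double lumen and product line are fully aliased. If calibre is instead entered as a linear term (10, 12, 14) with one combined tube-type indicator, the rank is 3 for 3 columns and the model is just identified. Its calibre slope then comes from CH10 versus CH12 alone, because the tube-type term absorbs CH14.

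**4. What CH10 versus CH12 can detect** (50 per arm from section 2.5.1; two-sided 5%, 80% power)

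- Mean NRS: d = (1.960 + 0.842)·√(2/50) = 0.560 SD by the normal approximation, and 0.566 SD with the t distribution. Both are just under 0.57 SD.
- Proportion with poor tolerance: the documents give no rate, so the reference rate p is an assumption. Solve for q, with p̄ = (p + q)/2, in

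 50 = {[1.960·√(2p̄(1−p̄)) + 0.842·√(p(1−p) + q(1−q))] / (q − p)}²

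| Assumed rate in one arm | Detectable rate in the other |
|---|---|
| 10% | 32.7% |
| 20% | 46.0% |
| 30% | 57.5% |

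These figures show how much information the unconfounded contrast carries. They do not measure the confounding itself.

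**The case against.** The strongest reply is that the formal secondary endpoint in section 1.3 asks about tube models, and randomised arms answer that question validly. Section 2.5.3 compares groups in exploratory terms and claims no calibre inference, so a misreading of its test is only predicted. Follow-up contrasts are also the kind of detail that a protocol article may leave to a fuller document.

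Much of this stands. Section 2.5.3 is not wrong as a comparison of devices, and the endpoint definition needs no change. What remains is that sections 2.2 and 2.5.1 state calibre as the question, section 3 anticipates the answer, and the only analysis described cannot supply it. That is a mismatch between a stated aim and the stated arms, and not merely a missing detail.

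A reader might infer three stronger points, none of which the documents support:

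- *That the CH14 comparisons are invalid.* They are sound randomised comparisons of tubes; only the attribution to calibre fails.
- *That the problem extends to aspiration success.* No section sets out to test whether calibre affects aspiration. Section 2.2 ties the aspiration feature of the CH14 tube to its extra lumen, and section 2.5.1 sets each tube against a 42% reference.
- *That the premise in section 1.1, "Through the use of NGTs that can guarantee greater aspiration performances with the same caliber", is false for CH14.* The introduction mentions 8–12 CH when describing small standard tubes that are hard to aspirate. It does not say that all standard tubes have that size, and the calibre of the hospital's current tubes is never given.

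**Conclusion.** The concern holds in a limited form. Sections 2.2, 2.5.1 and 3 frame tolerance as a matter of calibre, but a difference involving CH14 cannot be attributed to calibre, and the three-group test does not separate calibre from device. Only CH10 versus CH12 can address calibre, over a 2-CH step in 100 patients, and it can reliably detect only fairly large differences of about 0.57 SD in mean NRS. This rests on 50 evaluable patients per arm, on treating NRS as approximately continuous, and on CH10 and CH12 differing in nothing the documents leave undescribed. The detectable rates of poor tolerance depend on assumed reference rates.

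The point concerns the interpretation of one secondary endpoint. The primary endpoint and its sample size are unaffected. It should be corrected because it changes what the trial may conclude and costs almost nothing.

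**What to change.** 1. In sections 2.2, 2.5.1 and 3, reword the tolerance aim as a comparison of tube models, in line with section 1.3.
2. In section 2.5.3, state that any conclusion on calibre and tolerance rests on CH10 versus CH12 only, reported as a difference with its 95% confidence interval.
3. Label tolerance contrasts with CH14 as device comparisons, in which calibre, lumen number and product line change together.

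No new patients, visits or data are needed; the change is to wording, plus one pre-named contrast. The cost is a narrower calibre claim, limited to a 2-CH step in 100 patients, with modest effects likely to be missed.
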